**Methods:**

The study is a parallel-groups, randomised controlled trial examining the effectiveness and cost-effectiveness of iCBT interventions for depression and anxiety disorders, against a waitlist control group. The iCBT treatments are of 8 weeks duration and will be supported by regular post-session feedback by Psychological Wellbeing Practitioners. Assessments will be conducted at baseline, during, and at the end of the 8-week treatment and at 3, 6, 9, and 12-month follow-up. A diagnostic interview will be employed at baseline and 3-month follow-up. Participants in the waitlist control group will complete measures at baseline and week 8, at which point they will receive access to the treatment. All adult users of the Berkshire NHS Trust IAPT Talking Therapies Step 2 services will be approached to participate and measured against set eligibility criteria. Primary outcome measures will assess anxiety and depressive symptoms using the GAD-7 and PHQ-9, respectively. Secondary outcome measures will allow for the evaluation of long-term outcomes, mediators and moderators of outcome, and cost-effectiveness of treatment. Analysis will be conducted on a per protocol and intention-to-treat basis.

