#### Aims

The overarching aim of the present study is to implement and evaluate the long-term effectiveness & cost-effectiveness of internet-delivered interventions for depression and anxiety disorders within IAPT services. The specific research questions include the following:Are the SilverCloud *Space from Depression and Space from Anxiety* internet-delivered interventions in IAPT effective in treating depression and anxiety disorders, and maintaining outcomes at follow-up, compared to waiting-list groups?Are the SilverCloud *Space from Depression and Space from Anxiety* internet-delivered interventions cost-effective in treating depression and anxiety disorders in IAPT?Are mediators/mechanisms of change and maintenance associated with both post-treatment and long-term effectiveness of internet-delivered interventions for depression and anxiety?

We hypothesize that: a) the iCBT interventions will be more effective than the waiting-list group in treating depression and anxiety disorders; b) the iCBT interventions will be cost-effective compared to the waiting-list group in treating depression and anxiety; c) we expect that mediators/ mechanisms of change including, repetitive negative thinking styles, emotion regulation skills, therapeutic alliance, credibility and expectancy in iCBT, CBT skills usage and therapist behaviours will be identified as positively impacting post-treatment outcomes and maintenance of gains in iCBT.

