#### Trial design

A parallel-groups, randomised controlled trial design will be used to examine the effectiveness and cost-effectiveness of internet-delivered interventions for depression and anxiety disorders against a waiting list control group. Based on the primary diagnosis obtained from the Mini International Neuropsychiatric Interview 7.0.2 (M.I.N.I), participants will be randomised into one of two groups: one for depression and another for anxiety.

Randomisation will follow a 2:1 ratio. For ethical reasons, participants in the control group will receive access to the internet intervention after the waiting list period (8 weeks). The study will be conducted following the CONSORT statement [33], the CONSORT extension for web-based interventions (CONSORT-EHEALTH) [34] and the SPIRIT guidelines (Standard Protocol Items: Recommendations for Interventional Trials) [35]. The SPIRIT checklist can be found in Additional file 1. The study protocol, information on the study, informed consent, and trial related documents have been submitted and approved by the NHS England Research Ethics Committee [REC Reference: 17/NW/0311]. The study flowchart is shown in Fig. 1.

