##### Frequency of Actions and Thoughts Scale (FATS) [60]

The FATS is a 12-item scale, designed to assess the frequency with which CBT-related skills have been used during the previous week. Each item is measured on a 5-point scale (0 = not at all, 1 = one or two days; 2 = half the days; 3 = almost every day; 4 = every day). The FATS comprises four subscales, indicative of how much the person engaged in 1) cognitive restructuring, 2) social interaction, 3) rewarding behaviours and 4) activity scheduling in the past week; but also gives an overall score, indicative of overall CBT-related skills usages. Psychometric evaluations suggest high internal consistency of the total FATS scale (α = 0.86) and acceptable to high internal consistency of its subscales (α = 0.74 to 0.83). The FATS has been shown to be sensitive to change during iCBT and higher scores on the FATS have been linked to better treatment outcomes.

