#### Dropout measure

Finally, a *dropout questionnaire* will assess participants’ reasons for dropout from treatment. It includes only one open question asking for details about the specific reasons for dropout.

The study measures and assessment times are summarised in Table 2.

**Table 2 Tab2:** Study measures and assessment times

Measure	Assessment	Time of assessment
M.I.N.I. 7.0.2 for DSM-5	Diagnosis	BL and 3-FU
PHQ-9	Depression	BL, contin, Post-T, FU
GAD-7	Anxiety	BL, contin, Post-T, FU
IAPT Phobia Scale	Specific Phobia	BL, contin, Post-T, FU
WSAS	Functioning	BL, contin, Post-T, FU
SPIN	Social Phobia	BL, Post-T, FU
HAI	Health anxiety	BL, Post-T, FU
PSWQ	GAD	BL, Post-T, FU
PDSS	Panic	BL, Post-T, FU
EQ-5D-5 L	Health status	BL, Post-T, 6-FU, 9-FU, 12-FU
ReQol-10	Recovering quality of life/ mental wellbeing	BL, Post-T, 6-FU, 9-FU, 12-FU
CSRI	Resource utilisation	BL, Post-T, 6-FU
PEQ	Patient experience	Post-T
STAR-C	Therapeutic alliance	Throughout treatment, at each review of client
STAR-P	Therapeutic alliance	Throughout treatment, after each progress review with clinician
PBRS-A	Repetitive Negative Thinking	BL, week 4, Post-T, 3-FU
ERQ	Emotion Regulation	BL, Post-T
FATS	CBT-related skills usage	FU
Therapist behaviours checklist	Therapist behaviours	During treatment at review of client
Expectancy / credibility	Expectancy and credibility with the intervention	BL, week 4, Post-T
Dropout questionnaire	Reasons for dropout	3-FU

*BL* Baseline, *Post-T* Post-Treatment, *FU* All follow-ups, *3-FU* 3-month follow-up, *6-FU* 6-month follow-up, *contin* continuous, *PHQ-9* Patient health questionnaire-9, *GAD-7* Generalized anxiety disorder-7, *WSAS* Work and social adjustment, *SPIN* Social Phobia Inventory;` *HAI* Short health anxiety inventory, *PDSS* Panic disorder severity scale-self report, *PSWQ* Penn state worry questionnaire, *EQ-5D-5 l* EuroQol-5 Dimension-5 level, ReQoL-10 Recovering quality of life – 10 item version, *CSRI* Client services receipt inventory, *PEQ* Patient Experience questionnaire, *PBSR-A* Positive Beliefs about Rumination Scale – Adapted Version, *FATS* Frequency of Actions and Thoughts Scale, *ERQ* Emotion Regulation Questionnaire

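### CBT skills usage (FATS) is scheduled only at follow-up, so the post-treatment part of exploratory hypothesis (c) cannot be tested for it

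*Protocol article*

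**What the plan says.** Under Aims, hypothesis (c) lists several mechanisms and ends with the expectation that "CBT skills usage and therapist behaviours will be identified as positively impacting post-treatment outcomes and maintenance of gains in iCBT". It therefore covers two periods, the end of treatment and the time after it.

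The measure of CBT skills usage is the FATS, a 12-item scale with a one-week recall. The section describing it says: "The FATS has been shown to be sensitive to change during iCBT".

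Table 2 gives its assessment times in one row: "FATS CBT-related skills usage FU". The table note defines FU as all follow-ups and has separate codes for baseline and post-treatment. The abstract likewise lists assessments "at the end of the 8-week treatment and at 3, 6, 9, and 12-month follow-up", so the end of treatment is not one of the follow-ups.

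For controls, the abstract says: "Participants in the waitlist control group will complete measures at baseline and week 8". The sections Trial design and Waiting list control group both have them start the intervention at week 8.

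Two general sentences point another way. Client recruitment says that the primary and secondary outcomes are completed online after consent. Waiting list control group says that controls complete the primary and secondary measures at week 8. The FATS stands among the secondary measures.

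**The concern.** To say that skills usage helped to produce the post-treatment result, the trial needs a skills score taken no later than that result, and preferably before it. To say that the treatment raised skills usage, it needs a score in both randomised groups while the controls are still untreated, ideally with a baseline value. On the Table 2 schedule the FATS offers none of these.

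What is at stake is one stated secondary question. If the schedule and the hypothesis both stay as they are, a later report could relate follow-up FATS to the week-8 result and call it mediation, although the supposed mediator was measured after the outcome. No analysis method can repair this, because the data would not have been collected.

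**Working it through.** No formula or sample-size figure applies, and the plan gives no number to reproduce. The check sets the scheduled FATS occasions against two events, the week-8 outcome and the week-8 crossover.

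**Inputs**
- FATS occasions: follow-ups only (Table 2 and its note).
- Follow-up times: 3, 6, 9 and 12 months (abstract, Methods).
- Post-treatment outcome: end of the 8-week treatment (abstract, Methods).
- Untreated control occasions: baseline and week 8 (abstract; Waiting list control group).
- FATS recall period: the previous week (FATS section).

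**Step 1: when the first FATS is taken.** The article does not say whether follow-up months run from baseline or from the end of treatment. Three months is about 13 weeks.
- Counted from baseline: about week 13, which is 13 − 8 = 5 weeks after the post-treatment outcome.
- Counted from week 8: about week 8 + 13 = 21, which is 13 weeks after it.

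On either reading the first score comes after both the outcome and the crossover. With a one-week recall it covers roughly week 12 to 13 or week 20 to 21, and so does not reach back into the 8 weeks of treatment.

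**Step 2: count of scheduled FATS scores.**

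| Occasion | FATS scheduled |
|---|---|
| Baseline | 0 |
| During the 8 weeks | 0 |
| Post-treatment / week 8 | 0 |
| In untreated controls, at any time | 0 |

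**Step 3: what each part of the hypothesis needs.**
- *Post-treatment outcome.* There is no change score, no value before or at week 8, and no untreated comparison. It cannot be tested.
- *Maintenance of gains.* FATS at 3 months precedes PHQ-9 and GAD-7 at 6, 9 and 12 months, so the time order is right. There is no untreated comparison and no FATS baseline, so the result is an association only.

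**Step 4: comparison with the other mechanism measures.** Table 2 places the PBRS-A at baseline, week 4, post-treatment and 3 months, and expectancy/credibility at baseline, week 4 and post-treatment. The emotion-regulation row reads "ERQ Emotion Regulation BL, Post-T". Each has at least a baseline and a post-treatment value. The FATS has neither.

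**The case against.** **The table may be shortened by mistake.** The general sentences in Client recruitment and Waiting list control group would, read literally, put the FATS at baseline and week 8, and describing the scale as sensitive to change during treatment fits that reading. This stands as a reason to reconcile the text. It does not displace the explicit table row. The secondary heading also covers the patient experience questionnaire, the patient-rated alliance scale and the dropout questionnaire, which cannot sensibly be completed at baseline, so those sentences cannot mean every listed measure. If the FATS is in fact taken at baseline and week 8, Table 2 is wrong.

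**The protocol does not promise a randomised mediation analysis for every mechanism.** The research question asks only whether mechanisms are associated with effectiveness, and the same list includes alliance and therapist behaviours, which cannot exist in an untreated group. This is fair, and it means that the missing untreated comparison is not decisive alone. But even a plain association with the post-treatment outcome needs a score taken by then, and none is scheduled.

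**The work is exploratory.** Statistical analysis labels it so and says only what moderation and mediation analyses may use. This stands and limits the weight of the point.

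**A reader might infer that the FATS is useless here, or that emotion regulation has the same defect.** The documents support neither. The maintenance question remains open to the FATS. The ERQ has baseline and post-treatment values, so a change score exists and, with week-8 collection in controls, a randomised effect on it can be estimated. A week-4 ERQ would be a preference and is not asked for.

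**Conclusion.** The point holds in a limited form. As Table 2 stands, the FATS is collected on 0 of the 2 occasions at which an untreated comparison exists, and on no occasion up to and including the post-treatment outcome. The post-treatment part of hypothesis (c) therefore cannot be tested for CBT skills usage at any sample size. The maintenance part can be examined as an uncontrolled association.

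This rests on reading Table 2 as governing the schedule. It does not depend on where the follow-up months are counted from.

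It would go too far to infer that the mechanism aim as a whole fails or that the effectiveness result is at risk. The other mechanism measures discussed above have earlier scores, the analysis is exploratory, and the PHQ-9 and GAD-7 comparison, the sample size and the economic analysis do not use the FATS. The correction is worthwhile and cheap, but the trial's main conclusions do not depend on it.

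**What to change.** **Preferred change**
- In Table 2, add the FATS at baseline and at post-treatment/week 8 in both arms, within the online assessments already held then. This gives a change score and a randomised comparison of skills usage.
- Add it at week 4 in the treatment group alongside the PBRS-A, so that one score precedes the outcome. Ask for a week-4 value in the waiting list only if controls are already assessed then; the abstract gives them baseline and week 8 only.
- Keep the follow-up assessments.
- Reconcile Table 2 with the general statements in Client recruitment and Waiting list control group, saying which secondary measures are taken when.
- Recruitment began on 27 June 2017. Report how many participants enrolled before the change and so lack a baseline FATS. The document does not allow that number to be estimated.

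**Alternative.** Remove CBT skills usage from the post-treatment part of hypothesis (c), limit the FATS to maintenance, and describe that analysis as an association among treated participants.

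**Cost.** The preferred change adds 12 items per assessment: 2 × 12 = 24 per control and 3 × 12 = 36 per treated participant, plus an amendment to the schedule. The downside is slightly more respondent burden. The alternative is a change of wording only, but gives up the post-treatment question for this mechanism.

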##### Engagement and usage measures

The online system will collect anonymized descriptive data relating to engagement and usage of the service users with the platform. Data collected will include the number of modules completed, time spent in the platform, number of activities completed, number of minutes per log-in, number of sessions and length of sessions. A session is defined as an instance where a user logs on to the system. Session time will be always an imperfect calculation, as users may take breaks within a session, without formally log out of the system. To prevent this overestimation, periods of more than 30 min without interaction will be taken as one minute and periods of inactivity longer than 3 h will start the count on a new session. Use of different program components will be measured.

### Statistical analysis

The effectiveness of the internet-delivered interventions compared to control will be analysed using the intention to treat (ITT) approach. Participation levels will be monitored throughout the study and reasons for withdrawal or non-compliance of study subjects will be recorded to document bias associated with non-random protocol deviations. Any potential imbalances will be reported and considered fully in interpretation of the trial results. Missing data will be evaluated for randomness and imputed using multiple imputation procedures.

Differences in baseline primary and secondary outcome measures between treatment groups and waiting list control groups will be identified using χ^2^ tests for categorical variables and ANOVAs or t-tests for continuous variables. Efficacy of treatments over time will be measured using mixed effects models. To complement the post-hoc comparisons, the magnitude of change within and between the groups on the primary and secondary outcomes measures will be established using Cohen’s *d* statistic. Bonferroni corrected *p*-values will be reported for multiple comparisons. All statistical analyses will be conducted in SPSS, SAS and R. Results will be presented following CONSORT guidelines for reporting parallel group randomised trials.

The established IAPT definitions of recovery will be used in our analysis, where ‘recovery’ is determined by patients moving from ‘caseness’ at the beginning of the intervention (i.e. scoring ≥9 on the PHQ-9 or ≥8 on the GAD-7) to ‘non-caseness’ at the end of treatment (thus scoring below the cut-off). Two further established measures will be considered: *reliable improvement*, where the patient has a significant decrease in their PHQ-9 / GAD-7 score upon completion of their course of treatment; and *reliable recovery*, where the patient meets the criteria for both recovery and reliable improvement. Thus, a patient who moves from caseness to non-caseness, and does so by showing a significant decrease in their symptom scores, is said to have a reliable recovery [44].

Exploratory analyses, including the use of correlation and multiple regression, will be conducted to explore the role that mechanisms of change and maintenance measures play in the benefits obtained from the interventions. Moderation and mediation analyses may include the use of macros for SPSS and/or bootstrapping for exploring the role that mechanisms of change play on the outcomes.

Resource-use and subsequent costs will be estimated over the 12-month time horizon for the intervention group and for the 8-week waiting list time period for the control group. Healthcare resource will be valued using unit costs derived from available data sources [62–66].

For the purpose of the economic evaluation, EQ-5D-5 L and ReQoL-10 preference-based tariff score values will be used to elicit the quality adjusted life year (QALY) using the area under the curve (AUC) method to account for the collection of this data at multiple time points between baseline and 12-month follow-up in both trial-arms. The proposed economic analysis will be conducted for those with anxiety and those with depression separately and as a whole patient group. All economic analysis will be performed using Stata version 14 (or an updated version). Due to the shorter time horizon of the control groups (8 weeks based on a waiting list approach) compared to the intervention group (12 months with outcome assessment at 8 weeks, 6 months, 9 months and 12 months), methodological work will be carried out to assess the feasibility and uncertainty around extrapolating outcomes from the 8-week time period in the control group to a longer time horizon (e.g. 6-months, 9-months and 12-months) using survival analysis methods [67]. Cost per QALY analysis will be carried out over multiple time horizons (e.g. 8-weeks, 6-months, 9-months and 12-months) to address the uncertainty around decision making from using observed data (up to 8 weeks) and extrapolated outcomes (beyond 8 weeks) for the economic evaluation. Incremental mean point estimates of the difference in cost and QALYs between trial groups will be used to determine the incremental cost effectiveness ratio (ICER). ICER is defined here as the ratio between incremental costs and incremental effectiveness and the following formula will be employed:$$ ICER=\frac{\mathrm{Cost}\kern0.5em \mathrm{active}\kern0.5em \mathrm{intervention}\kern0.5em \mathrm{group}\hbox{-} \mathrm{Cost}\kern0.5em \mathrm{control}\kern0.5em \mathrm{intervention}\kern0.5em \mathrm{group}}{\mathrm{Efectiveness}\kern0.5em \mathrm{or}\kern0.5em \mathrm{Utility}\kern0.5em \mathrm{active}\kern0.5em \mathrm{intervention}\kern0.5em \mathrm{group}\kern0.5em \hbox{-} \mathrm{Efectivenes}\kern0.5em \mathrm{or}\kern0.5em \mathrm{Utility}\kern0.5em \mathrm{control}\kern0.5em \mathrm{intervention}\kern0.5em \mathrm{group}}. $$

Statistical bootstrapping will be used to plot the cost-effectiveness acceptability curves (CEACs) for the purpose of describing the probability of cost-effectiveness of the intervention compared to usual care at willingness-to-pay thresholds normally used by decision makers (i.e. £20,000 per QALY). One-way sensitivity analysis will be used to describe the uncertainty around these estimates. If the trial results suggest there is considerable uncertainty around the cost-effectiveness of the intervention, a simple economic decision model will be designed to inform an expected value of information (EVI) analysis. These EVI results can be used to suggest the upper bound cost of future research around this area of care.

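### The ICER is built from differences in group-mean AUC QALYs with no baseline-utility adjustment named, although baseline carries half the weight of the 8-week comparison

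*Protocol article*

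**What the plan says.** All of this is in the Protocol article, mainly under Statistical analysis.

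- **QALYs.** EQ-5D-5L and ReQoL-10 utilities are turned into QALYs "using the area under the curve (AUC) method to account for the collection of this data at multiple time points between baseline and 12-month follow-up". Table 2 schedules both measures at "BL, Post-T, 6-FU, 9-FU, 12-FU", so baseline is the first point of the curve.
- **ICER.** "Incremental mean point estimates of the difference in cost and QALYs between trial groups will be used to determine the incremental cost effectiveness ratio". The printed formula is the active group's value minus the control group's value, for cost and for effect. No baseline covariate is named for either.
- **Horizon.** Control data are observed for 8 weeks only, and anything later is extrapolated. The analysis is run for each disorder separately and for both together.
- **Uncertainty.** Bootstrapping supports the acceptability curves, with £20,000 per QALY as the example threshold.
- **Baseline comparison.** "Differences in baseline primary and secondary outcome measures between treatment groups and waiting list control groups will be identified using" chi-square tests for categorical variables and t-tests or ANOVAs for continuous ones.
- **Clinical outcomes.** "Efficacy of treatments over time will be measured using mixed effects models". How baseline enters these models is not stated.

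**The concern.** An AUC QALY that starts at baseline includes a quantity the intervention cannot have changed. If one randomised group happens to begin with higher utility, its QALY total is higher for that reason alone, and a plain difference in group means cannot separate this from the treatment effect. Over a year the baseline point is a small part of the curve. Over 8 weeks with two assessments it is half.

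At stake is the only cost-per-QALY comparison that rests on observed data in both groups, and with it the starting point for the extrapolation to 6, 9 and 12 months. The expected QALY gain over 8 weeks is so small that ordinary chance imbalance can be of similar size.

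The planned baseline tests do not help. Under valid randomisation any difference is due to chance, so a p-value answers no open question, and a non-significant result does not show that an imbalance is too small to matter.

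**Working it through.** **Group sizes (stated in Sample size, reproduced).** With d = 0.5, two-sided alpha 0.05, 80% power and 2:1 allocation, the normal approximation gives 48 controls: 1.5 × (1.960 + 0.842)² / 0.25 = 47.1, rounded up. With 96 treated this is 144 per disorder (noncentral t power 80.2%). Then 2 × 144 = 288, and 288 × 1.25 = 360, which is 120 v 60 per disorder and 240 v 120 pooled.

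**Assumptions.** The article gives no utility SD, baseline-to-week-8 correlation r, or utility effect. I assume SD 0.15-0.25 (equal at both times), r 0.5-0.7, and a week-8 gain of 0.05 (also 0.02-0.10).

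**AUC weight.** Over 8 weeks the trapezoid gives baseline and week 8 a weight of 0.5 × 8/52 = 0.0769 years each.

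**Imbalance through the baseline point.** SE of the baseline difference = SD × √(1/n₁ + 1/n₂), multiplied by 0.0769 for QALYs.

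| Groups | SD | SE, utility | 1 SE in QALYs |
|---|---|---|---|
| 120 v 60 | 0.15 | 0.0237 | 0.0018 |
| 120 v 60 | 0.20 | 0.0316 | 0.0024 |
| 120 v 60 | 0.25 | 0.0395 | 0.0030 |
| 240 v 120 | 0.15 | 0.0168 | 0.0013 |
| 240 v 120 | 0.25 | 0.0280 | 0.0022 |

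**Gain to compare it with.** 0.05 × 0.0769 = 0.0038 QALY, or £77 at £20,000 per QALY. Gains of 0.02-0.10 give 0.0015-0.0077. One SE of imbalance at 120 v 60 is worth £36-61.

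**Carry-over to week 8.** Baseline utility predicts week-8 utility, so the expected total contribution of an imbalance is (1 + r) times its direct one. At SD 0.20 and r = 0.5: 0.0316 × 0.0769 × 1.5 = 0.0036 QALY.

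**Effect of adjustment.** The unadjusted QALY variance is proportional to 2 + 2r. After regression on baseline utility it is proportional to 1 − r². The SE ratio is √[(2 + 2r)/(1 − r²)] = √[2/(1 − r)], which is 2.0 at r = 0.5 and 2.6 at r = 0.7.

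- At 120 v 60 the SE falls from 0.0032-0.0056 to 0.0013-0.0026 QALY.
- With a true gain of 0.00385, the chance that the estimated difference has the wrong sign, Φ(−gain/SE), falls from 11-25% to 0.2-7%. Pooled, it falls from 4-17% to under 2%.

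**What a baseline t-test would detect.** At 120 v 60 only an observed difference of about 0.31 SD reaches p < 0.05. At SD 0.20 that is 0.062 in utility, and 0.062 × 0.0769 = 0.0048 QALY. An imbalance worth more than the assumed gain could therefore pass as non-significant.

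**The case against.** The strongest reply is that this is a condensed article. Incremental means and a generic ICER formula are compatible with regression-adjusted increments, and covariates are often left to a health-economic analysis plan. That stands in part: the text never calls the differences raw or unadjusted, so adjustment is not excluded. But the method that is printed is a difference of group values, and a more precise one is available from data already collected.

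The bootstrap is a second reply. It carries the sampling variation from chance imbalance into the acceptability curves, so the uncertainty is shown. That also stands. Resampling does not, however, remove the observed imbalance from the point estimate, and the uncertainty stays wider than it need be. The pooled analysis is less exposed, as the table shows.

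Several stronger readings are tempting and are not supported:

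- **That the plan tests baseline instead of adjusting for it.** The mixed models may carry baseline as a covariate or as an occasion. Its role is unspecified, not refused.
- **That power is lost on PHQ-9 and GAD-7.** This would require the efficacy analysis to be an unadjusted week-8 comparison. The two-group calculation was used for sizing, while mixed models are planned for analysis, so no loss is shown.
- **That imbalance will be handled by interpretation alone.** The sentence on reporting imbalances follows text on withdrawal and non-compliance and does not clearly concern baseline scores.
- **That false alarms are likely and will steer conclusions.** Ten measures in two disorders would give 1 − 0.95²⁰ = 64% for at least one significant result, but only if the tests were independent. These measures are correlated, and no analysis depends on the test results.
- **That the QALY comparison is biased.** Under randomisation the unadjusted difference is unbiased on average. The bias is conditional on the imbalance that occurs.

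**Conclusion.** The point holds as a worthwhile improvement that needs no new data, not as an error that invalidates the economic analysis. As printed, the 8-week QALY difference is exposed to chance baseline imbalance of the same order as the effect sought. Adjustment would roughly halve its standard error or do better. The weights and group sizes come from the article. The QALY amounts rest on the assumed SD, correlation and gain and scale with them. No size is given for the cost side, because the article offers no cost variance.

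The baseline tests are a secondary matter: explicitly planned and uninformative, but harmless so long as nothing depends on them.

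**What to change.** In the economic analysis, state that incremental QALYs are estimated by regression on the baseline value of the same utility measure (EQ-5D-5L or ReQoL-10), and incremental costs by regression on baseline CSRI cost. Fit both regressions within each bootstrap resample used for the acceptability curves, and use the adjusted increments in the ICER.

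In the clinical analysis, replace the baseline significance tests with descriptive summaries by group. State that baseline enters the mixed models either as a covariate or as an occasion with a mean constrained to be common to the groups.

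The cost is wording. Table 2 already schedules PHQ-9, GAD-7, EQ-5D-5L, ReQoL-10 and CSRI at baseline. The choice should be fixed before outcomes are compared by group, so that adjustment cannot be decided after the imbalance has been seen.

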#### Sample size

Sample size was determined separately for primary presentations of anxiety disorders and depression for the trial. Using the software program G-power [36] and based on a moderate between group effect size of *d* = 0.5 with a power of 80%, an alpha error of 0.05, and a 2:1 randomisation procedure into immediate treatment and a corresponding waiting list control group. This calculation returned a total sample of 144 participants in the depression arm (96 in the treatment group and 48 in the WL group) and the same for anxiety, leading to a total of 288 participants. To ameliorate against attrition, a 25% uplift was added, resulting a total sample size of 360. Therefore, this number translates to a ratio of *n* = 120 in the treatment group and a corresponding *n* = 60 in the control group for depression, and the same ratio for anxiety. The 2:1 randomisation procedure was implemented to reduce the likelihood of having many people waiting for treatment after presenting to the IAPT service.

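### Bonferroni correction is valid, but Holm's step-down would hold the same 0.05 family-wise error rate with more power on the second and later comparisons: an optional, cheap improvement

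*Protocol article*

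**What the plan says.** The Statistical analysis section gives the main efficacy method in one sentence: "Efficacy of treatments over time will be measured using mixed effects models". Effect sizes are then added: "To complement the post-hoc comparisons, the magnitude of change within and between the groups on the primary and secondary outcomes measures" are to be expressed as Cohen's d. The multiplicity rule follows directly: "Bonferroni corrected *p*-values will be reported for multiple comparisons". The section does not say which comparisons form a family or how many there are. On software it says "All statistical analyses will be conducted in SPSS, SAS and R".

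The Sample size section sizes depression and anxiety separately. Each calculation is "based on a moderate between group effect size of *d* = 0.5", "with a power of 80" per cent and "an alpha error of 0.05", and gives 96 treated and 48 waiting-list participants per disorder. The Trial design section confirms the allocation: "Randomisation will follow a 2:1 ratio". The alpha in this calculation is not divided for multiple comparisons.

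**The concern.** Bonferroni tests each of m comparisons at 0.05/m, whatever the other comparisons show. Holm orders the p-values and tests the smallest at 0.05/m, the next at 0.05/(m − 1), and so on, stopping at the first failure. Its family-wise guarantee is the same and needs no further assumption. As a rule for deciding which hypotheses to reject, it rejects everything that Bonferroni rejects and sometimes more.

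This trial has reason to care about the later rejections. It names two primary measures, the PHQ-9 and GAD-7, and many secondary measures, and its first research question covers both disorders and maintenance of outcomes. What is at stake is modest: a real effect that is not the strongest in its family may be missed when the same family-wise limit would have allowed it to be declared.

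**Working it through.** **Inputs from the protocol article.** d = 0.5, power 80%, alpha 0.05, 2:1 allocation, 96 v 48 per disorder.

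**Assumptions, not in the article.** Two-sided tests; family size m = 2 or 4; correlation 0.6 between the test statistics (0.3 to 0.8 for the range); normal (z) test statistics; unless stated otherwise, every true effect is d = 0.5.

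**Step 1: reproduce the stated sample size.** With two controls' worth of treated participants per control, n(control) = (1 + 1/2) × (1.960 + 0.842)² / 0.5² = 1.5 × 7.85 / 0.25 = 47.1, rounded up to 48. Treatment is 2 × 48 = 96 and the total is 144, as stated. The noncentral-t power at 96 v 48 is 80.2% two-sided. One-sided it would be 87.9%, so the stated figure fits a two-sided test. It is a calculation for one comparison at 0.05 and involves neither Bonferroni nor Holm.

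**Step 2: why Holm's p-values are never larger.** Bonferroni multiplies every p-value by m. Holm multiplies the j-th smallest by (m − j + 1) and takes the running maximum. Each multiplier is at most m, so each adjusted value is at most the Bonferroni one. As an illustration with m = 2 and p-values 0.02 and 0.04: Bonferroni gives 0.04 and 0.08; Holm gives 0.04 and max(0.04, 0.04) = 0.04. The smallest p-value is treated identically, so the two methods always agree on whether anything at all is rejected.

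**Step 3: Bonferroni power by formula.** The mean of the z statistic is 0.5 × √(96 × 48 / 144) = 0.5 × √32 = 2.83.
- m = 2: critical value 2.24, power Φ(2.83 − 2.24) = Φ(0.59) = 72%.
- m = 4: critical value 2.50, power Φ(2.83 − 2.50) = Φ(0.33) = 63%.

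**Step 4: Holm against Bonferroni by simulation** (1,000,000 draws, correlation 0.6, all effects real):

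| m | Quantity | Bonferroni | Holm |
|---|---|---|---|
| 2 | average power per comparison | 72% | 77% |
| 2 | both rejected | 60% | 70% |
| 2 | at least one rejected | 84% | 84% |
| 4 | average power per comparison | 63% | 72% |
| 4 | all four rejected | 36% | 57% |
| 4 | at least one rejected | 86% | 86% |

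At m = 2, the gain in power for both is about 9 to 11 points over correlations 0.3 to 0.8.

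**Step 5: when not all effects are real** (correlation 0.6).
- m = 2, one real effect: power for that effect is 72% under both methods (a difference of about 0.1 points). Realised family-wise error is 2.5% under Bonferroni and 4.0% under Holm.
- m = 4, three real effects: realised family-wise error is about 1.3% under Bonferroni and 3.2% under Holm.
- No real effects: family-wise error is the same for both methods, 0.045 at m = 2 and 0.040 at m = 4. The expected number of false rejections stays at 0.05 under Bonferroni and is about 0.055 to 0.057 under Holm.

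Holm's family-wise error stayed below 0.05 in every setting tried.

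**The case against.** The strongest reply is that Bonferroni is a valid, pre-stated correction with strong family-wise control under any dependence. Its cost is conservatism, not bias or inflated error, so this is a preference between two valid methods. That stands, and it is why the point is an optional improvement and not a correction.

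A reader might infer that the trial gives up power for nothing. The documents and the arithmetic do not support that. Bonferroni has lower realised error when some nulls are true, bounds the expected number of false rejections at 0.05, and has simple matching simultaneous confidence intervals. The article promises corrected p-values and does not mention such intervals. It is condensed, though, and does not rule them out.

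A reader might also infer that the stated 80% power is undermined. It is not: that figure is for one comparison at 0.05 and is the same whichever correction is used.

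The objection to the size of the gain also stands in part. The article gives neither m nor the correlation. The power figures assume that every effect is real, which is Holm's best case, and the article nowhere sets joint rejection of all comparisons as its objective. Waiting-list participants start treatment at week 8, so an untreated 96 v 48 contrast does not exist at the later follow-ups, and the model does not describe comparisons at those times or within groups.

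What remains is that, for deciding which hypotheses to reject, Holm never does worse than Bonferroni at the same family-wise level and needs no extra assumption.

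**Conclusion.** The point holds as a modest efficiency gain. For the reported adjusted p-values, Holm keeps the 0.05 family-wise limit and can only add rejections. If all effects are d = 0.5 with 96 v 48 and correlation 0.6, average power per comparison rises by about 5 points at m = 2 (72% to 77%) and about 9 points at m = 4 (63% to 72%). The family sizes, the correlation and the assumption that all effects are real are the reviewer's and not the article's. The chance of at least one rejection and the sample size of 144 per disorder are unaffected, and the gain almost vanishes when only one effect in the family is real. No result or statement in the plan is wrong as it stands.

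**What to change.** In the multiplicity sentence of the Statistical analysis section, or in the analysis plan, specify Holm step-down adjusted p-values in place of Bonferroni, applied within the same families of comparisons, and settle this before the analysis. R and SAS, both already named, can compute them. If simultaneous confidence intervals are to be reported, keep Bonferroni for the intervals and say that intervals and p-values may then disagree at the margin.

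The cost is one sentence of wording, with no new data and no more participants. The price in error control is that more of the 0.05 allowance is used when some nulls are true. If the sponsor prefers Bonferroni for its simplicity or its intervals, keeping it is defensible.
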